## Abstract

**Background:**

Bacterial vaginosis (BV) is estimated to affect 1 in 3 women globally and is associated with obstetric and gynaecological sequelae. Current recommended therapies have good short-term efficacy but 1 in 2 women experience BV recurrence within 6 months of treatment. Evidence of male carriage of BV-organisms suggests that male partners may be reinfecting women with BV-associated bacteria (henceforth referred to as BV-organisms) and impacting on the efficacy of treatment approaches solely directed to women. This trial aims to determine the effect of concurrent male partner treatment for preventing BV recurrence compared to current standard of care.

**Methods:**

StepUp is an open-label, multicentre, parallel group randomised controlled trial for women diagnosed with BV and their male partner. Women with clinical-BV defined using current gold standard diagnosis methods (≥3 Amsel criteria and Nugent score (NS) = 4–10) and with a regular male partner will be assessed for eligibility, and couples will then be consented. All women will be prescribed oral metronidazole 400 mg twice daily (BID) for 7 days, or if contraindicated, a 7-day regimen of topical vaginal 2% clindamycin. Couples will be randomised 1:1 to either current standard of care (female treatment only), or female treatment and concurrent male partner treatment (7 days of combined antibiotics - oral metronidazole tablets 400 mg BID and 2% clindamycin cream applied topically to the glans penis and upper shaft [under the foreskin if uncircumcised] BID). Couples will be followed for up to 12 weeks to assess BV status in women, and assess the adherence, tolerability and acceptability of male partner treatment. The primary outcome is BV recurrence defined as ≥3 Amsel criteria and NS = 4–10 within 12 weeks of enrolment. The estimated sample size is 342 couples, to detect a 40% reduction in BV recurrence rates from 40% in the control group to 24% in the intervention group within 12 weeks.

**Discussion:**

Current treatments directed solely to women result in unacceptably high rates of BV recurrence. If proven to be effective the findings from this trial will directly inform the development of new treatment strategies to impact on BV recurrence.

**Trial registration:**

The trial was prospectively registered on 12 February 2019 on the Australian and New Zealand Clinical Trial Registry (ACTRN12619000196145, Universal Trial Number: U1111–1228-0106, https://www.anzctr.org.au/Trial/Registration/TrialReview.aspx?id=376883&isReview=true).

## Background and rationale

Bacterial vaginosis (BV) affects 1 in 3 women globally [1] and increases the risk of important gynaecological and obstetric sequelae including preterm delivery, spontaneous abortion STI and HIV acquisition [2–5]. The global economic burden of treating BV is estimated at USD$4.8 billion annually, with an even greater burden if associated sequelae are included [1]. Current recommended first line treatment for BV is with metronidazole or clindamycin [6], delivered as oral or vaginal therapies for 7 days, with equivalent 1-month BV cure rates of 80% [7], but only 50% of women have been shown to maintain an optimal vaginal microbiota (VM) 3–6 months post-treatment [8]. More effective treatment strategies are needed to improve BV cure, restore and sustain an optimal VM and to reduce adverse health outcomes globally [9].

Evidence that sexual transmission contributes to the pathogenesis of BV has been reported since the 1950s, and led to six male partner treatment trials in the 1980s and 90s [10, 11]. Treatment regimens for males in these trials differed and included oral metronidazole (2 g single dose, 2 g on days 1 and 3 or 500 mg twice daily [BID] 7 days), single dose oral tinidazole (2 g), or oral clindamycin (150 mg four times a day [QID] 7 days) [12–17], with a number of non-standard regimens with respect to current practice. Women were treated with similar regimens to their partner. Only one trial demonstrated a significant impact of partner treatment on recurrence (men received oral metronidazole 2 g single dose vs placebo) [14], and as a consequence, partner treatment was not adopted in clinical practice [10, 18, 19]. However, reviews of the early partner treatment trials also highlighted the significant issues that render their findings inconclusive [10, 18, 19]. Since the publication of these partner-treatment trials, an increasing body of epidemiological data shows women with a regular partner are more likely to experience post-treatment recurrence compared to women with no partner or a new post-treatment partner [8, 20, 21], and microbiological data supports transmission or exchange of BV-associated bacteria (henceforth referred to as BV-organisms) during sexual activity [22–27]. Notably, BV-organisms are more prevalent in the sub-preputial space (under the foreskin) and distal urethra of male partners of females with BV than without BV [22, 26], and recently, the composition of the meatal microbiota was shown to be particularly predictive of incident BV in female partners [24]. A biofilm dominated by BV-organisms has also been detected in male urine and semen more commonly in male partners of females with BV than without BV [28]. Both sexual activity and male circumcision have been shown to influence the penile microbiota [23, 29, 30], with male circumcision prospectively associated with a significant reduction in BV-organisms and a reduction of BV in their female partners [30–32]. Women with a circumcised partner can still develop BV [33] indicating that the sub-preputial space is not the only reservoir of BV-organisms. Collectively this body of evidence suggests that carriage of BV-organisms at both urethral and penile skin sites in men is providing a reservoir from which BV-organisms can be reintroduced to treated women rendering current female treatment strategies inadequate.

The optimal approach to promote clearance of BV-organisms from male partners is, however, unknown. We hypothesise that in order to promote clearance of BV-organisms from both anatomical sites in males, a combination of oral and topical antibiotic therapy may be required. Metronidazole is a nitroimidazole antibiotic with activity against anaerobic bacteria including several BV-organisms such as *G. vaginalis*, *Prevotella* spp., *Bacteroides* spp., *Porphymonas* spp., and *Fusobacterium* spp. [34, 35]. Clindamycin is a lincosamide antibiotic with broad spectrum activity against Gram-positive cocci as well as anaerobic Gram-positive and Gram-negative bacteria [36]. We propose that BV-organisms in the distal urethra of males may be best targeted by oral antibiotics such as metronidazole, while those in the sub-preputial space and coronal sulcus may be most effectively cleared by a topical antibiotic, such as clindamycin cream, which is more suited than a gel to cutaneous application. The additional of topical therapy is also likely to be particularly important in uncircumcised males who have high abundance of sub-preputial BV-organisms [22, 23, 30, 32]. It is possible that the failure of prior male partner treatment trials to include topical antimicrobial therapy contributed to their lack of benefit in women.

### Objectives

In this publication we describe the protocol of a randomised controlled trial (RCT) with the aim to reduce BV recurrence in the female. The primary objective is to determine whether the concurrent treatment of male partners with combined oral metronidazole and topical clindamycin cream (*Intervention group*) reduces the risk of BV recurrence compared to current standard of care, female treatment only (*Control group*), within 12 weeks of enrolment. We hypothesise that male partners who are concurrently treated with antibiotics at the same time as their partner will be less likely to re-infect them with BV-organisms, and their partner will be less likely to experience recurrence within 12 weeks of enrolment compared to women undergoing female treatment only.

### Trial design

This is an open-label, multicentre, parallel-group RCT. Couples assessed for eligibility and recruited will be randomised 1:1 to either the *Intervention group* or *Control group* as described above.

The Standard Protocol Items: Recommendations for Interventional Trials (SPIRIT) checklist is provided as Additional file 1.

## Methods

### Study setting

Women will be recruited in three Australian states from sexual health centres (the Central Co-ordinating site, Melbourne Sexual Health Centre [MSHC], Victoria, and Sydney Sexual Health Centre [SSHC], New South Wales [NSW]), and Family Planning centres (Victoria, NSW, South Australia). Women will also be able to be referred from primary care (General practice, GP) or self-refer to the study if they have seen trial posters or the trial website. All women, regardless of recruitment site, will be assessed for clinical-BV prior to enrolment, as described below. Figure 1 illustrates participant flow throughout the trial.

**Fig. 1 Fig1:**
[figure not shown]
Participant flow through the study from recruitment to study endpoint. ^1^been together ≥8 weeks, indicated/confirmed on phone that RSP likely to participate; ^2^refer to eligibility criteria; ^3^protocol violation means not in modified intention-to-treat (mITT) primary analysis or per protocol analysis; ^4^eligible for mITT and per protocol analyses if week 4 and/or 12 provided but with missing data, not eligible for safety analysis; ^5^if female participant does not attend clinic visits but does return a swab, eligible for secondary endpoints; ^6^if female attends at week 4 but not week 12, still be eligible for mITT; if no visits but returns a swab, eligible for secondary endpoints; if no visits or swabs, protocol violation. Abbreviations: LTFU, Loss to follow up; W, withdrawn

### Participants

#### BV diagnosis methods

The combination of both ≥3 Amsel criteria and a NS = 4–10 will be used to diagnose BV in this trial. This reflects clinical practice and diagnosis of the symptomatic syndrome of BV. Amsel criteria [37] include: i) presence of a characteristic homogenous vaginal discharge; ii) elevated vaginal pH > 4.5; iii) positive amine test (noticeable fishy odour); iv) ≥20% clue cells (epithelial cells coated by adherent gram-negative rods) on microscopy. The Nugent method scores bacterial morphotypes on vaginal Gram stain [38]: i) NS = 0–3 represents a lactobacillus-dominant “optimal” VM, ii) NS = 4–6 represents an intermediate state with few lactobacilli and increased anaerobes, and iii) NS = 7–10 is classified as Nugent-BV. Combining a NS = 4–10 with at ≥3 Amsel criteria optimises the clinical diagnosis of symptomatic BV and importantly captures Amsel positive women with an intermediate NS. Recruitment of women at sites where microscopy is not available will be based on the presence of three Amsel criteria at the bedside: i) presence of a characteristic homogenous vaginal discharge; ii) elevated vaginal pH > 4.5; and iii) fishy odour. A slide for Gram stain of high-vaginal secretions will be collected from women at these sites and sent to MSHC for Nugent scoring and for visualisation of clue cells, and women with NS = 0–3 will be classified as *Screening failures* (see definitions below).

#### Eligibility criteria

Females will be eligible for recruitment if they fulfil the following criteria: are aged 18 years to pre-menopausal (defined as still menstruating within the last 12 months); *and* have symptomatic BV as defined above; *and* have a regular male partner for the prior 8 weeks who is willing and eligible to participate; *and* are being treated with a first line recommended antimicrobial therapy for BV as defined above; *and* have sufficient English language proficiency to understand the study requirements; *and* provide written informed consent; *and* are willing and able to comply with protocol requirements including clinic visits at 4 and 12 weeks; *and* do not have any of the exclusion criteria listed below.

Males nominated as the regular sexual partner of a woman fulfilling inclusion criteria will be *eligible* if they are aged 18 years or above; *and* enrol within a week of their partner with confirmed BV; *and* have sufficient English language proficiency to understand the study requirements; *and* provide written informed consent; *and* are able to comply with protocol requirements; *and* do not have any of the exclusion criteria or contraindications listed for metronidazole.

Prospective participants will be ineligible if they meet any of the following exclusion criteria: are a current sex worker; *or* have concurrent sexual partners; *or* are known to be HIV positive. *Additionally,*
*females*
*will be excluded if they:* are being currently treated for pelvic inflammatory disease with 14 days of metronidazole with/without ceftriaxone *or* are not being treated with first line recommended antimicrobial therapies for BV at baseline *or* are pregnant or breast feeding; *or* have hypersensitivity or a contraindication to all first line drugs used to treat BV: nitroimidazoles and clindamycin (note they can be enrolled if they are able to take one of these agents). *Additionally,*
*males*
*will be excluded if they:* have hypersensitivity or a contraindication to *either* nitroimidazoles or clindamycin; *or* if they have significant fungal balanitis.

#### Contraindications

In addition to exclusion criteria above, participants should not be prescribed metronidazole if they have one of the following contraindications: cannot abstain from alcohol during treatment; *or* have a history of epilepsy or central nervous system disorders that predispose to seizures; *or* are known to have peripheral neuropathy; *or* are known to have severe liver disease; *or* are known to have a prolonged QT interval on ECG; *or* are known to have a low neutrophil count; *or* are currently taking warfarin, lithium, disulfiram, phenytoin, phenobarbitone, busulphan, or cimetidine.

### Intervention

All female participants will receive oral metronidazole 400 mg twice daily for 7 days, or if contraindicated, a 7-day regimen of topical vaginal 2% clindamycin cream.

#### Intervention – concurrent male partner treatment

Male partners randomised to the *Intervention Group* will receive concurrent male partner treatment of combined oral metronidazole 400 mg BID and topical 2% clindamycin cream to be applied to the glans penis and upper shaft (under the foreskin if uncircumcised) BID for 7 days.

#### Control – female treatment only (current standard of care)

Male partners randomised to the *Control Group* will not receive treatment and the control for the trial is the current standard of female treatment only. The twice daily application of a topical placebo for 7 days to the penile skin would be highly likely to influence bacterial composition/microbiota. Due to the concerns of this impact on the effect estimate a decision was made against providing a topical placebo to males randomised to the control group.

Adherence will be measured via questionnaire the day following antibiotic therapy (day 8). Participants can discontinue trial treatment and remain in the trial. They can also withdraw from the follow-up assessments at any time.

### Outcome measures

The primary outcome is BV recurrence using current gold standard diagnostic methods defined as ≥3 Amsel criteria and Nugent score (NS) = 4–10 within 12 weeks of enrolment. The secondary outcomes are i) BV recurrence defined as NS ≥ 7 within 12 weeks, ii) BV recurrence defined as ≥3 Amsel criteria within 4 weeks, iii) BV recurrence defined as NS ≥ 7 within 4 weeks, iv) recurrence of a microbiota dominated by BV-associated bacteria within 12 weeks, and v) recurrence of a microbiota dominated by BV-associated bacteria within 4 weeks. All Amsel criteria endpoints require a clinic visit whereas Nugent endpoints can be evaluated using specimens collected at home (see Table 1). Additional measured outcomes include i) adherence to antibiotic therapy (by both women and men), ii) acceptability of antibiotic therapy to men, and iii) adverse effects (AEs) in men (safety analysis).

**Table 1 Tab1:**
[figure not shown]
Schedule of enrolment, intervention, assessments and specimen collection

Key: C = clinic visit - required for females only, men may complete at home, H = home procedures; AEs = adverse effects. ^a^required for females only, ^b^a slide containing vaginal secretions is collected for Nugent score; ^c^specimens added to preservative and stored for future molecular studies, ^d^male sample collection at home will be aligned with female samples

### Sample size

BV recurrence rates after recommended therapy are high. Sobel et al reported 50% recurrence within 3 months, and our group reported 52% recurrence within 6 months [8, 39]. We have chosen 12 weeks of follow up, as we believe this will be the optimal duration over which to measure the direct effect of treatment of the male partner on BV recurrence and minimises the risk of introduction of new untreated partners into the “treated partnership”. To obtain an estimate of the efficacy that we could expect from male partner treatment, we have used the reduction in risk reported from consistent condom use (50%) [8, 20] and male circumcision (40–60%) [31]. Based on our data we assume a 12-week BV recurrence rate in the control group of 40%, and conservatively estimate that treating male partners will reduce the risk of BV recurrence in females by 40%. This effect size is at the lower end of that reported from consistent condom use and circumcision.

Data indicate that women with an IUD in situ are more likely to experience BV recurrence [40, 41]. We hypothesise this is due to BV-organisms and biofilm persisting on the IUD after antimicrobial therapy. We will therefore limit recruitment of women with an IUD to no more than 20% of the total study population (68 women/couples), and this will be reviewed at the interim analysis.

With a total sample size of 290 heterosexual couples (145 per arm), we will have 80% power to detect a 40% reduction in BV recurrence from 40% in the control group to 24% in the intervention group (2-alpha = 5%). Assuming a 12-week loss to follow up of 15% in keeping with our previous trials, 342 couples will be recruited (171 couples per arm) to allow for a well-powered primary analysis.

### Participant timeline

#### Recruitment of women with BV

All prospective female participants will first be assessed for BV by a clinician at one of the trial sites. For sites with an onsite laboratory, diagnosis of BV using both Amsel and Nugent criteria will be conducted onsite. For clinicians at one of the sites without an onsite laboratory, a “diagnostic kit” will be provided to standardise clinical diagnosis. The “diagnostic kit” includes the provision of MColorpHast™ vaginal pH indicator strips (pH 2.0–9.0; Merck KGaA, Darmstadt, Germany), a “diagnostic checklist form” to document presence or absence of three Amsel criteria (BV discharge, malodour and pH > 4.5), and a swab and slide for Gram stain of vaginal secretions, that is sent for Nugent scoring and identification of clue cells at the central co-ordinating site. For all women with 3/3 Amsel criteria who are recruited at a site without an onsite laboratory, if the vaginal Gram stain is subsequently scored as NS = 0–3, then the woman will be deemed as a *Screening Failure,* as defined below. When BV is confirmed, women will be referred to the research team and undergo screening procedures.

The trial research nurse will assess eligibility, explain full trial procedures and obtain written consent. Prior to commencing medication, all women will complete a baseline questionnaire, self-collect a high vaginal swab and arrange a time for the research team to contact their partner.

#### Recruitment of male partners

After a recruited woman confirms with the research team that her partner is interested in participating in the trial, a time will be made to speak with him (either immediately if he is present in clinic or via a telephone recruitment consultation). The research nurse will first provide a detailed explanation of the trial, check for trial eligibility and any contraindications to medication, with review by a clinician as required prior to randomisation. For all males, once trial and medical eligibility have been documented in an electronic medical record, written informed consent will be obtained. *For a male present in person* this will be written informed consent from the outset. *For a male on the phone*, initial verbal consent will be documented in the electronic medical record, and then written informed consent will be obtained by return of the signed PICF with the baseline recruitment pack. Following consent, randomisation will be performed. If a male is randomised to the *intervention group*, he will be instructed on how to use the medication. All male participants, regardless of randomisation group will be instructed to collect baseline genitourinary samples (urine and penile skin sample) and refrain from any sexual contact for the 7 days that their partner is taking medication (or, while they are taking their medication if randomised to the *Intervention group*). Study material (i.e. specimen collection materials and questionnaires) and medication (if randomised to the *Intervention group)* will be provided in person or will be couriered to the participant’s home.

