### Allocation

Allocations will be generated by an independent biostatistician, with study investigators blinded to the randomisation sequence. A 1:1 randomisation ratio to standard of care (female treatment only, *Control group*) or female partner treatment with concurrent male partner treatment (*Intervention group*), in blocks of size four-six, will be used with stratification by recruitment site and known risk factors for recurrence: intrauterine device (IUD)-use and circumcision status. After obtaining verbal consent, the research nurse will log into a password-protected online database, REDCap, an electronic data capture tool hosted and managed by Helix (Monash University) [42], to complete screening and eligibility assessments. The randomisation allocation button will only be visible once all the required information has been entered and the couple are deemed eligible. REDCap will then retrieve the next ‘sealed’ allocation from within each recruitment site and either the IUD-user or non-IUD user stratified allocation and then within these two groups, an uncircumcised or circumcised stratified allocation.

If a protocol violation occurs after randomisation (defined above), reasons will be collected and the participant will be deemed either lost to follow up or withdrawal if this is formally what they decide to do. Couples who fail screening will not be included in the evaluable population for analyses and therefore the next “sealed” allocation can be used to recruit an additional couple.

As this is an open-label RCT, both the research nurse performing randomisation and the participants will know which group they are in. However, the microscopists performing Nugent scoring, clue cell reporting and amine testing will be blinded to randomisation group.

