#### Baseline procedures

Once eligibility has been assessed and consent forms signed, participants will be instructed on self-collection of high-vaginal swabs and vaginal secretions on a slide for NS, penile swabs, and urine samples (Table 1, Fig. 2), and provided with a baseline questionnaire. A clinician and pharmacist will instruct participants about antibiotic use and AEs. Couples will be asked to avoid alcohol and to abstain from sex during treatment.

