### Data safety and monitoring

Females receive first line recommended antibiotic therapies, which have been used extensively for decades with an excellent safety profile for the treatment of BV. Metronidazole is also used in a broad range of non-genital anaerobic infections. All female and male participants are assessed for contraindications and drug interactions prior to enrolment. In this study, males are being treated for an indication that is outside approved indications but with Australian Therapeutic Goods Administration (TGA) authorisation (CT-2019-CTN-00046-1). Safety assessments post-treatment will be focused on AEs and symptom-directed assessments. The Trial Management Committee (TMC), consisting the Lead Principal Investigator (PI), co-ordinating PI, and research nurses, will assess whether AEs are thought to be study drug-related and then report relevant cases to the Alfred Hospital Human Research Ethics Committee (HREC) and compile them for the Data Safety Monitoring Board (DSMB), comprising two clinicians with knowledge of sexual health and an independent statistician. The DSMB will review any AEs and advise the Trial Steering Committee (TSC), consisting the lead PI, co-ordinating PI, trial statisticians and epidemiologists, on how to move forward.

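### Men recruited by phone can be randomised on verbal consent before the signed form that makes them eligible comes back, so exclusions from the primary analysis can depend on arm

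*Protocol article*

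**What the plan says.** The Eligibility criteria section lists, among the conditions a man must meet, that he "provide written informed consent". The Baseline procedures section keeps the same order: "Once eligibility has been assessed and consent forms signed, participants will be instructed on self-collection". The Allocation section adds a gate: "The randomisation allocation button will only be visible once all the required information has been entered and the couple are deemed eligible".

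For a man on the phone, the Recruitment of male partners section describes two stages. Verbal consent is recorded first, and then "written informed consent will be obtained by return of the signed PICF with the baseline recruitment pack. Following consent, randomisation will be performed". The last sentence does not say which of the two consents is meant. The Allocation section does say: "After obtaining verbal consent, the research nurse will log into a password-protected online database, REDCap", and it is in that database that eligibility is completed and the allocation is drawn.

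Three other statements matter. The Allocation section says that the randomising nurse and the participants know the arm. The recruitment section says that study material, with medication for intervention men, is handed over or couriered. Item iv of the Protocol violation section makes a man's failure to supply baseline specimens, questionnaire or signed PICF a violation, and violations are ineligible for the primary mITT and per protocol analyses.

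**The concern.** The text lets a couple be randomised before the man meets a stated entry criterion. That is an internal contradiction whatever its statistical effect.

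The statistical effect runs through item iv of the Protocol violation section. Returning the signed form and the baseline pack becomes something a phone-recruited man does after he knows his arm, and whether he does it can decide whether his partner's outcome is counted in the primary analysis. A man who has learned that he will receive no treatment may have less reason to post the pack than a man who has been given treatment. If return rates differ by arm, and the women in non-returning couples have a different risk of recurrence, the compared groups are no longer the groups that were randomised.

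**Working it through.** **Order of steps for a man recruited by phone**

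| Step | Section | What it implies |
|---|---|---|
| Written consent needed to be eligible | Eligibility criteria | Signed form before the couple is eligible |
| Button shown only for eligible couples | Allocation | Signed form before allocation |
| Forms signed before baseline instruction | Baseline procedures | Signed form before the baseline pack is completed |
| Database opened after verbal consent | Allocation | Allocation can precede the signed form |
| Signed form returned with the baseline pack | Recruitment of male partners | Signed form comes with or after baseline collection |
| Missing form is a violation, not a screening failure | Protocol violation; Screening failure | A randomised couple without a signed form is foreseen |

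The first three rows and the last three cannot all hold for these men. Two details favour the later rows as the working procedure. The instruction to collect baseline samples is given to men whatever their randomisation group, so it follows allocation. The Allocation section also provides for violations that arise after randomisation.

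**Plan's own figures**

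The Sample size section assumes 40% v 24% recurrence, two-sided 5% and 80% power. The usual two-proportion formula gives 133 per arm. With the continuity correction it gives 145 per arm, which is the stated 290. Allowing for loss, 290 / (1 − 0.15) = 341.2, rounded up to the stated 342. These figures reproduce and are not in dispute. The planned difference is 40 − 24 = 16 points.

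**Illustration of size**

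The documents give no rate of unreturned forms, so everything here except the 40% is an assumption. Suppose there is no true effect, with recurrence p = 0.40 in both arms. A fraction L of an arm is excluded, and the excluded women recur at rate r. The observed risk among those kept is

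(p − L × r) / (1 − L).

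| Loss, control v intervention | r | Control | Intervention | Control minus intervention |
|---|---|---|---|---|
| 10% v 2% | 0.60 | 0.340/0.90 = 37.8% | 0.388/0.98 = 39.6% | −1.8 points |
| 10% v 2% | 0.20 | 0.380/0.90 = 42.2% | 0.396/0.98 = 40.4% | +1.8 points |
| 15% v 5% | 0.60 | 0.310/0.85 = 36.5% | 0.370/0.95 = 38.9% | −2.5 points |
| 15% v 5% | 0.20 | 0.370/0.85 = 43.5% | 0.390/0.95 = 41.1% | +2.5 points |

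The sign follows r: the same losses can hide a benefit or create one. These losses apply to whole arms, but only phone-recruited men are affected and their share is not given. If, say, half were recruited by phone, 10% v 2% becomes 5% v 1%. With r = 0.60 the risks are 0.370/0.95 = 38.9% and 0.394/0.99 = 39.8%, a gap of about 0.9 points.

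**The case against.** **Staged consent has an evident reason.** Partner treatment is to be concurrent with the woman's, and a man must enrol within a week of her. His verbal consent is documented after eligibility checks. An ethics committee may have accepted this, and an article may leave consent workflow to the full protocol. That explains the procedure, but the sections as printed still contradict each other.

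**Consent before randomisation could mean written consent.** The recruitment section alone allows that reading. The Allocation section names verbal consent, and the violation list foresees a randomised couple with no signed form, so the reading does not survive for phone recruits.

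**The bias comes from the analysis set, not from the order of steps.** This largely stands. The woman gives her own written consent and attends her own visits, so a missing male form does not by itself stop her outcome being measured. It is lost to the primary analysis because of item iv. That item can also be read as applying only when all three items are missing, which would make exclusions rarer. Moving consent forward would not cure everything either: baseline specimens and male withdrawal before day 8 remain post-allocation events that exclude the couple.

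**Stronger inferences that the documents do not support.**
- A reader might infer that men take medication without ever signing, the more seriously because "males are being treated for an indication that is outside approved indications". No section says that medication leaves before the form returns. It follows only from the absence of a step that withholds it.
- A reader might infer that such men's adverse-effect data are unusable. The Protocol violation section says that violations may still be eligible for other analyses, and the Statistical methods section includes every man who took at least one dose.
- A reader might infer that men's baseline samples have no timing rule. The schedule is in Table 1 and Fig. 2, which are not shown, and the surviving key aligns men's home samples with women's.

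**Conclusion.** The point holds for men recruited by phone. The sections on eligibility, recruitment, allocation and baseline procedures give incompatible orders for signed consent and randomisation. Because the arm is known and item iv of the Protocol violation section excludes couples on what the man returns, exclusions from the primary mITT analysis can depend on arm.

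Neither the size nor the direction of any bias can be determined from the documents. Under assumed whole-arm losses of 10% v 2% to 15% v 5%, and assumed recurrence of 20% or 60% in the excluded women, it is about 1.8 to 2.5 points either way. It is smaller if only some men are recruited by phone, and modest beside the planned 16 points. The documents do not show that the trial's conclusion would be overturned. The case for change rests on the contradiction and on how easily the arm-dependent exclusion can be avoided.

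**What to change.** 1. Make the man's signed PICF (electronic signature, or a scanned or photographed form) and his completed baseline questionnaire required REDCap fields, so that the allocation button cannot appear without them. The button is already conditional on required information. Refusals then fall before allocation, where they cannot unbalance the arms.
2. Reconcile the Eligibility criteria, Recruitment of male partners, Protocol violation, Allocation and Baseline procedures sections so that they give one order of steps. State whether one missing item or all three trigger item iv.
3. For what can still go missing after allocation, namely baseline specimens and male withdrawal before day 8, keep the consenting woman's outcome in the primary analysis as randomised, as far as consent to data use allows. Report any remaining exclusions by arm with reasons.

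The cost is an electronic or scanned consent step in a system already in use, a wording amendment and ethics notification. Whether the ethics committee would accept that form of signature is not in the documents. The downside is a short delay for phone-recruited men, which has to fit the one-week enrolment window, and some couples lost before rather than after randomisation.
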